#### **6.4.2 Contraindications**

The system is not intended for:

- Use in gestation period < 21 completed weeks
- Use in multiple pregnancies
- Use on patients with dermatologic diseases in which abdominal skin is involved
- Use on patients connected to external or implanted stimulators
- Use during defibrillation, electrosurgery or magnetic resonance imaging (MRI)
- Use in x-ray departments

#### **6.4.3 Safety**

NRM Link, NRM Link Charger and NRM App are parts of Nemo Remote® (NRM). Nemo Remote® is classified as class IIb, following Rules 10 and 11 of Chapter III of Annex VIII as well as implementation rules 3.3 and 3.5 of the Medical Device Regulation EU Regulation 2017/745.

Nemo Remote® complies with the following standards:

- EN 15223-1:2016
- EN ISO 20417:2021
- EN ISO 14971:2019
- IEC 60601-1:2005+AMD1:2012+AMD2:2020
- IEC 60601-1-2:2014+ AMD1:2020
- EN 60601-1-6: 2010+A1:2015
- IEC 60601-1-11:2015/AMD1:2020
- EN 62304:2006+A1:2015
- IEC 82304-1:2016
- EN 62366-1:2015+A1:2020
- Regulation (EU) No 207/2012

Nemo Patch is an accessory of Nemo Remote®, classified as Class I medical device according to rule 1 of Annex VIII of the Medical Device Regulation EU Regulation 2017/745.

The Nemo Patch complies with the following standards:

- EN 15223-1:2016
- EN 1041:2008 + A1:2013
- EN ISO 14971:2012
- EN 62366-1:2015
- EN ISO 10993-1:2018

#### 6.4.4 Clinical warnings and potential risks

- The system is not a replacement for observation and evaluation of the patient and fetus at set times by a qualified healthcare provider, who makes diagnoses and takes decisions regarding treatment and interventions. For accurate care of the patient and fetus, clinical assessment of the CTG should be combined with knowledge of patient anamnesis and risk factors.

- The system is not designed for:
  - Use during defibrillation, electrosurgery or magnetic resonance imaging (MRI)
  - Use in x-ray departments.

Remove the Patch prior to performing any of the above scenarios, otherwise harm to the patient or damage to equipment may occur.

- From 27 to 36 weeks gestational age, the chance of FHR signal loss is higher due to the presence of vernix caseosa, which can reduce transmission of electrical signals.
- In case clinical decision-making cannot be properly substantiated based on the CTG registration, other observation and monitoring methods must be used.
- In some cases, the use of the Patch, in combination with skin prep, may result in skin irritation. Try to reduce the duration of use and the skin prep as far as possible if the skin is irritated.
- To prevent reduced performance, replace a Patch when its adhesive properties have reduced or the electrode gel has come partially loose.
- To prevent cross-contamination, never reuse a Patch on another patient.
- To prevent the risk of skin irritation, ensure that no cleaning or disinfection agent residues remain on the system.
- The system detects repeating characteristics of the fetal and maternal ECG signal to calculate the fetal and maternal heart rate. If either the pregnant woman or her fetus has a highly irregular ECG, the heart rate may not be calculated correctly and the system may temporarily provide incorrect output. In case clinical decision-making cannot be sufficiently substantiated, other observation and monitoring methods must be used.
- In rare cases, the amplitude of the fetal ECG signal that is measured on the maternal abdomen is in the same order of magnitude as the amplitude of the maternal ECG that is being measured. In these circumstances, interchange of fetal and maternal heart rate may occur. The system will then temporarily display FHR values as maternal heart rate and maternal heart rate values as FHR. In case clinical decision-making cannot be sufficiently substantiated, other observation and monitoring methods must be used.
- The system is developed to detect FHR from extremely small fetal ECG signals in electrical measurements that may contain significant amounts of noise. The system evaluates the quality of the fetal ECG component in the measured signals. When the fetal ECG quality is too low to reliably detect the FHR, the FHR output is suppressed. In case clinical decision-making cannot be sufficiently substantiated, other observation and monitoring methods must be used.
- To prevent incorrect output, the system continuously evaluates the quality of the FHR output. If the FHR output repeatedly has not passed this quality check over a certain period of time, the FHR output is suppressed. In case clinical decision-making cannot be sufficiently substantiated, other observation and monitoring methods must be used.

- The system detects uterine activity based on electrohysterography (electrical activity of the uterine muscle). In limited cases, the registration may show deviations from the baseline that are not related to actual contractions, when compared to an intra-uterine pressure catheter. In case clinical decision-making cannot be sufficiently substantiated, other observation and monitoring methods must be used. Nemo Remote - Technical Brochure 7
- The system only provides qualitative information about uterine activity and no information about pressure.
- The measurement of abdominal fetal ECG, as performed by the system, is based on extremely small signals. For optimum measurement of these signals, the Link contains sensitive components that are subject to technological limitations. To prevent incorrect measurements through external electromagnetic interference, it is recommended to avoid using equipment that emits electromagnetic radiation in the vicinity of these measurements.
- The system shall only be used if the tablet is configured by mobile device management to ensure data privacy and guarantee the performance of the system.

[removed for publication]

*Figure 7. Physical Specifications – Nemo Remote® Link and Link charger*

[removed for publication]

*Figure 8. Physical Specifications. Nemo Remote® App*

[removed for publication]

*Figure 9. Physical Specifications: Nemo Remote® accessories*

[removed for publication]

*Figure 10. Environmental Specifications*

## 7. METHODS

### 7.1 Study parameters/endpoints

#### 7.1.1 Main study parameter

To assess the primary objective of successful remote eCTG monitoring, definitions of successful measurement are as follows:

- Minimum of 30 minutes eCTG registration (32);
- Including overall a maximum of 20% signal loss (32);
- Sufficient interpretability according to HCPs clinical interpretation, if not maximum extended until 90 minutes when reassuring but insufficient.

Criteria defining a successful measurement is described in a standard operating procedure (SOP) and will be available for (trained) HCPs at the hospital to avoid prematurely closing of the eCTG registration. The precise duration of monitoring in minutes, the amount of signal loss in percentage and the duration of signal loss in minutes will be derived from the recordings during the analysis phase of the project, i.e. not during the measurements.

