**Study population:** Pregnant patients (N=60) >18 years old with a singleton, high-risk pregnancy from 32 until 37 weeks of gestational age. High-risk is defined as: diagnosed with PE, FGR, PPRM, or others with an indication for fetal monitoring at least twice a week, these patients are eligible for inclusion in this study. The main exclusion criteria are: suspected labor within 48 hours, severe pre-eclampsia, umbilical artery Doppler with absent- or reversed flow, external- or implanted electrical stimulator and language barrier.

**Intervention:** Remote eCTG monitoring (using Nemo Remote®), daily in a Home@Hospital setting for 30-90 minutes, or at least twice weekly at the outpatient clinic. Monitoring duration depends on signal quality and interpretability of the eCTG tracing, and lasts at least 30 minutes, and will be ceased after 90 minutes if the eCTG signal quality and/or interpretability is then still insufficient. In 24 patients ultrasound clips of 2 x 5 minutes of the uterine and umbilical artery Doppler will be collected simultaneously to the eCTG measurements.

**Main study parameters/endpoints:** Primary outcome: The percentage of successful eCTG measurements in a Home@Hospital setting. This will be defined as the necessity to switch to conventional CTG based on the amount of signal loss. Secondary outcomes: Automated interpretation of the eCTG, maternal and perinatal outcomes, patient and healthcare professional satisfaction and costs. Additional outcome: Feasibility of synchronized multimodal acquisitions of maternal and fetal measurements.

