### Remote electrophysiological cardiotocography monitoring (eCTG) – Nemo Remote® (NRM)

Due to the limitations of conventional CTG monitoring, extensive research has been carried out to develop new, non-invasive, monitoring methods. Remote eCTG – including NI-fECG – monitoring has shown to be a very promising technique (17-20). This technique uses a wireless and beltless electrode patch that is placed on the maternal abdomen (Figure 1). It monitors fetal heart rate (FHR) by fetal electrocardiography (fECG), maternal heart rate by maternal electrocardiography, and the electrical activity of the uterine muscle by electrohysterography (EHG) (21-24). The electrophysiological recordings are hardly affected by maternal or fetal movement or abdominal wall thickness, as they are transferred through conduction of electrical signals across the underlying tissues (13, 25). Furthermore, the wireless electrode patch on the maternal abdomen gives patients the ability to move (16). The HASTA study will evaluate the feasibility of self-administered home monitoring in a Home@Hospital setting for a selected groups of complicated pregnancies. Feasibility will be evaluated by assessing the success rate (percentage of successful measurements) of remote eCTG, and whether no switch to conventional CTG due to interpretability is needed. Success rate is defined as maximum of 20% signal loss of total recorded time or at least 30 minutes of sufficient CTG interpretability. For further description see sections 2.1 and 7.1.1.

[figure not shown][figure not shown]

*Figure 1. eCTG including NI-fECG – Nemo Remote® (NRM)*

Furthermore, the FHR obtained from the fetal ECG measurements collected through NRM in this study will be used to check if the algorithm of the FHR – developed during labor – can also benefit for premature fetus. Automated interpretation of fetal monitoring could lead to improved prevention in the future. In addition, the effects of self-administered remote eCTG monitoring in a Home@Hospital setting on maternal and perinatal outcomes, patient and HCP satisfaction, and costs will be evaluated.

Besides feasibility of eCTG, this study will additionally evaluate the feasibility of synchronized multimodal acquisitions of maternal and fetal measurements as a first step towards the development of a prediction model.

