### 5.1 Investigational treatment

All patients will receive routine care following national guidelines and/or local protocols. Participants at the clinic will receive self-administered remote eCTG monitoring by NRM once a day (*Figure 1*). In case of follow-up at the outpatient clinic, participants will receive self-administered remote eCTG monitoring by NRM once per day or at least twice a week, depending on their care path. The realtime eCTG measurement will be instantly transferred digitally to the hospital electronic patient file (Chipsoft HiX) and assessed real-time on interpretability by the HCP. Monitoring will last between 30-90 minutes depending on the interpretability and reassurance of the remote eCTG measurement. Criteria defining a successful measurement are described in a standard operating procedure (SOP) and will be available for HCPs at the hospital to avoid prematurely closing of the eCTG measurement (see section 7.1.1). All HCPs involved in this study will receive training on the study protocol. The study procedure and statistical analysis are described in section 7.3.2, chapter 9 and in *Figure 12*.

Monitoring will be repeated the same day when reassuring but insufficiently interpretable, or upon request of the HCP in case of concerns about maternal and/or fetal condition. Additional detailed information of the NRM is described under investigational product (chapter 6). When remote eCTG interpretability is insufficient – based on clinical assessment of HCPs – a switch to conventional CTG monitoring will take place. In this study, HCPs will be asked to define clearly if a switch to conventional CTG was made based on insufficient interpretability or because of concerns about fetal and/or maternal condition (section 7.1.2).

From the second day onward, synchronized US Doppler measurements (clips of 2 x 5 minutes) of the umbilical and uterine arteries will be performed simultaneously with the remote eCTG for 24 patients ([images removed]

*Figure 3*). Measurements of two groups - cardiovascular low (PPROM; N=12) versus cardiovascular high-risk (PE/FGR; N=12) - will be collected and analyzed to evaluate the feasibility of synchronized multimodal acquisitions of maternal and fetal measurements.

[images removed]

*Figure 3. Measurement fetal and maternal heartrate, Doppler arteria umbilicalis, Doppler uterine artery and uterine activity.*

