- Once the eCTG measurement is considered successful – or when the maximum of 90 minutes has exceeded – the HCP will send a message in the Luscii app® and will contact the participant by telephone a few minutes later, the time they have stopped the remote eCTG measurement. All findings will be discussed with the participant and completed in the patients' file in HiX. In addition, the HCP will visit the participant in the hospital room.
- When eCTG measurement is not successful but reassuring, the measurement will be repeated the same day on a moment agreed between participant and HCP (PA).
- When eCTG measurement is not interpretable after repetition on the first day of inclusion, eCTG will be defined not successful – primary outcome – and a switch to conventional CTG will take place. Equally to routine care, in- hospital care is needed and home- monitoring will not be possible.
- When after an additional clinical visit by the HCP (PA) “unscheduled consult” at participants room for other reasons than signal quality concerns (e.g. contractions, reduced fetal movements, patients concerns), without indication for hospitalization – eCTG adequate and reassuring – participants can continue “home monitoring” through eCTG like it will be once home monitoring is implemented in the future. No switch to conventional CTG will be needed. This additional visit will be recorded as part of the patient journey for later cost analysis purposes (*Figure 11, Table 2*).
- As long as remote eCTG measurements are successful, participants will continue the study interventions until discharge, delivery or when 37 weeks is reached. At any moment – when demanded by the participants or by the HCP – a switch to conventional CTG will be made.
- When reached a GA of 37 weeks, after delivery or at discharge, participants will be asked to fill in a second digital questionnaire (5.1, 7.3.3), and at 4 weeks after delivery a third questionnaire.

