## 9. STATISTICAL ANALYSIS

### 9.1 Primary study parameter(s)

Primary data statistical analyses will be performed using SPSS version 29 (IBM Corp., Armonk, NY, USA) and SAS software version 9.4 (SAS Institute Inc., Cary, NC, USA). Signal quality will be defined as the percentage of time (minutes) in which the remote eCTG device delivers an FHR value. Signal quality will be determined for each patient. Mean, SD, and 95% confidence interval (CI) of the mean success rate will be calculated using a one-sample t-test. The one-way ANOVA analog, Kruskal-Wallis test will be used in when no normal division of outcomes is found. Success rate will be defined as the number and percentage (N/%) of remote eCTG registration the first day of inclusion with at least 30 minutes interpretable signal quality and/or less than 20% signal loss during 30 to 90 minutes measurement (see section 7.1.1).

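### The definitions of the primary outcome disagree on a day-1 recording ended before 30 minutes for maternal or fetal concern, and no rule settles how it counts

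*Protocol*

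**What the plan says.** The protocol describes success or failure of the day-1 recording in several places:

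- **7.1.1** lists three conditions: "Minimum of 30 minutes eCTG registration (32"; "Including overall a maximum of 20% signal loss (32"; and interpretability in the judgement of the healthcare professional (HCP). No exception is made for the reason a recording ended.
- **9.1** counts as successful a first-day recording with "at least 30 minutes interpretable signal quality and/or less than 20% signal loss during 30 to 90 minutes measurement".
- **Summary**, on the primary outcome: "This will be defined as the necessity to switch to conventional CTG based on the amount of signal loss".
- **Section 1**: "Success rate is defined as maximum of 20% signal loss of total recorded time or at least 30 minutes of sufficient CTG interpretability".
- **7.3.2**: "When eCTG measurement is not interpretable after repetition on the first day of inclusion, eCTG will be defined not successful". The outpatient procedure has the same rule.

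On stopping early, 7.3.2 says: "At any moment – when demanded by the participants or by the HCP – a switch to conventional CTG will be made". Under 5.1 the HCP must "define clearly if a switch to conventional CTG was made based on insufficient interpretability or because of concerns about fetal and/or maternal condition". These reasons, and premature closures, become secondary counts in 7.1.2.

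On repeats, 2.1 and 4.4 let a second same-day recording decide the primary outcome when the first was reassuring but technically inadequate. Section 5.1 also allows a same-day repeat at the HCP's request because of maternal or fetal concern, without saying whether it counts.

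Section 7.4 lets investigators withdraw a participant for urgent medical reasons. Section 7.5 provides for replacement only before study interventions begin. Neither states the effect on the denominator of the primary rate.

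**The concern.** The primary question is technical: can women obtain a usable eCTG tracing themselves? A recording can be short because the signal was poor, or because the HCP acted on something clinical while the signal was good. Only the first bears on that question. The 30-minute condition in 7.1.1 and 9.1 does not separate the two, and the recorded reason that could do so is not carried into the primary classification.

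Because the other descriptions of the outcome lead elsewhere, the same woman could be a failure, a success, unclassified or absent. With 60 participants, one or two such women change the headline rate visibly. If the rule is left open, it may be chosen with the results in view.

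**Working it through.** **Step 1. One case against each description.** Take an interpretable day-1 recording with almost no signal loss, ended after 15 minutes for maternal or fetal concern.

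| Section | Condition applied | Result |
|---|---|---|
| 7.1.1 | At least 30 minutes, at most 20% loss, interpretable | Not successful: 15 < 30 |
| 9.1, first branch | At least 30 interpretable minutes | Not met |
| 9.1, second branch | Under 20% loss in a recording of 30 to 90 minutes | Not met: recording too short |
| Summary | Switch because of signal loss | Not a failure |
| Section 1, first branch | At most 20% loss of recorded time, no minimum duration | Success |
| 7.3.2 | Uninterpretable after repetition | Failure rule does not apply; unclassified |
| 7.4 | Withdrawal for urgent medical reasons | Possibly absent |

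**Step 2. The plan's own figures.** Section 4.4 gives N = 60, an expected success rate of 90%, which it calls clinically sufficient, and a lower 95% limit of 82.5%. The simple (Wald) formula n = z²p(1−p)/d², with z = 1.96, p = 0.90 and d = 0.075, gives 61.5, close to 60. The Wilson interval that the section names has a lower limit of 79.9% at 54/60. That mismatch is a separate matter. Here only N = 60 and the 90% figure are needed.

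**Step 3. Effect of one case.** 1/60 = 1.7 percentage points.

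**Step 4. Assumed range.** The protocol gives no frequency for such stops. Assume 54 of 60 recordings are technically good and k of those 54 were ended before 30 minutes for concern. The rate is (54−k)/60 if they count as failures, (54−k)/(60−k) if they are left out, and 54/60 if they are judged on signal up to the stop.

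| k | Failures | Left out | Judged on signal |
|---|---|---|---|
| 1 | 53/60 = 88.3% | 53/59 = 89.8% | 90.0% |
| 2 | 52/60 = 86.7% | 52/58 = 89.7% | 90.0% |
| 3 | 51/60 = 85.0% | 51/57 = 89.5% | 90.0% |
| 4 | 50/60 = 83.3% | 50/56 = 89.3% | 90.0% |

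For k = 2 the two-sided 95% Wilson intervals are 75.8–93.1%, 79.2–95.2% and 79.9–95.3%.

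**Step 5. A different baseline.** Assume 54 successes among the other recordings and 3 early clinical stops. The rates are 54/60 = 90.0% (failures), 54/57 = 94.7% (left out) and 57/60 = 95.0% (judged on signal). All three reach 90%, so whether the rule decides the comparison with 90% depends on the rest of the data.

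**The case against.** A reader might infer that the protocol counts these recordings as device failures. It does not say so anywhere. That result follows from 7.1.1 and 9.1 read literally, while the summary, section 1, 7.3.2 and 7.4 permit other results. One can reply that section 1 and 9.1 both refer to 7.1.1, so 7.1.1 governs. That is a fair reading, but the summary and the failure rule in 7.3.2 still do not match it.

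A reader might also infer that such a woman gets no second recording. Section 5.1 allows one at the HCP's request when there is concern. What is missing is whether it counts.

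Nor do the documents show that such stops are common, or that subgroup rates for PE, FGR or PPROM are biased by them. Section 4.3 excludes women in whom an obstetric intervention is expected within 48 hours, for example because of a non-reassuring CTG or active blood loss. Section 4.2 requires that no exclusion criterion be present more than 24 hours after admission. Section 7.3.2 needs no switch after an unscheduled consultation when the eCTG is adequate and reassuring and hospitalization is not indicated. What remains is concern arising during the first 30 minutes of a day-1 recording. This is less common, but not ruled out.

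Finally, handling of early stops is often left to a statistical analysis plan, and the success criteria also sit in a standard operating procedure; neither is shown. Duration, signal loss and switch reason are all collected, so the cases can be identified later. This limits the weight of the point but does not remove it, because the protocol itself defines the primary outcome and does so in ways that disagree.

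**Conclusion.** The point holds as a conflict of definitions. Under 7.1.1 and 9.1 a day-1 recording shorter than 30 minutes cannot be successful, even with good signal and a clinical reason for stopping. The summary, section 1, 7.3.2 and 7.4 lead to different classifications, and nothing links the recorded switch reason to the primary outcome.

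The certain part of the size is 1.7 points per case at N = 60. The rest is assumed: with 54 technically good recordings and 2 early clinical stops, the choice of rule moves the rate from 86.7% to 90.0%, a spread of 3.3 points. The intervals overlap widely. It does not follow that the choice will decide whether 90% is reached; it can from the first assumed baseline and does not from the second. The matter is worth settling before the results are seen, because it affects the headline rate and is inexpensive to settle.

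**What to change.** 1. Reconcile the summary, section 1, 7.1.1, 7.3.2 (both procedures) and 9.1 into one success definition, including whether its conditions are joined by and or by or.
2. State in 7.1.1 and 9.1 that a day-1 recording ended before 30 minutes, with maternal or fetal concern recorded as the reason under 5.1, stays in the denominator and is classified by signal loss and interpretability up to the stop.
3. Say whether a same-day repeat prompted by concern counts toward the primary outcome.
4. Report the number of such recordings, and give the primary rate with all of them counted as failures as a bound.

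The cost is a few sentences and one sensitivity line, since the reason, duration and signal loss are already collected. The downside is that a few classifications will rest on short traces with no minimum length, which is open to debate; the bound shows how much depends on them. The change concerns outcome classification only and leaves every clinical decision to switch as it is.

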## **2. OBJECTIVES**

### **2.1 Primary objective**

The primary objective of this study is to assess the percentage of successful self-administered remote eCTG (including NI-fECG ) measurements in a Home@Hospital setting. This will be defined based on the percentage of signal loss and total duration of adequate registration and will be assessed on the first or – when indicated – the second eCTG measurement on the first day of inclusion. When the first remote eCTG measurement is reassuring but insufficient, the measurement will be repeated the same day.

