#### **4.4 Sample size calculation**

In a previous cohort study for conventional remote CTG monitoring, 4% of all tracings needed repetition (562 out of 12,649) and 0.9% (N=111) of the CTGs had to be repeated in the hospital. The success rate at first trace was 95.5% and after repetition 99% (28) .

A success rate of 90% is considered clinically sufficient based on previous studies (28-30) and HCPs' opinion. Only the first day of remote eCTG measurements will be used for determination of the feasibility by assessing the signal quality and success. If the remote eCTG measurement is technically insufficient but reassuring – according to current clinical policy – it can be repeated once at the same day and still be considered successful. Calculated on 90% chance of success according Wilson standard error of proportions (CI95% > lower limit of 82.5%), 60 subjects are needed for inclusion in this cohort study.

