#### 7.1.2 Secondary study parameters

##### *Remote eCTG parameters*

- Number of days with remote monitoring per participant.
- Number of remote eCTG measurements per participant.
- Need to repeat remote measurements the same day because of reassuring but insufficient interpretability.
- Number of switch to conventional CTG and possible maternal and/or fetal reason.
- Number of switch to conventional CTG needed because of poor signal of remote eCTG measurement and possible cause.
- Success rate of CTG measurement after switch based on same criteria as in remote eCTG monitoring (7.1.1).
- Incidence of skin irritation.
- Number of “unscheduled visits” and reason.
  - When there is an indication for an additional visit in-hospital as if the participant is monitored at home (e.g. contractions, decreased fetal movements, PE symptoms, suspicion of PPRM).
- Number of “re-admissions” and reason.
  - When there is an indication of admission as if the participant is monitored at home (e.g. blood loss, threatened premature labor, hypertension with indication for intravenous medication).
- The number of eCTG measurements assessed successful at closure by HCP.
- The number of eCTG measurements prematurely closed by HCP before complying the criteria of a successful measurement (7.1.1).

- Maternal and fetal factors HCPs have included in their assessment of the eCTG measurement (e.g. GA, fetal growth, Doppler measurements, PPRM).

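### The same-day repeat is decided live but signal loss is scored later, so under 7.1.1 a recording accepted at closure can become a failure that can no longer be repeated, while other sections would not count it as one

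*Protocol*

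**What the plan says.** - **Success criteria.** Protocol 7.1.1 lists at least 30 minutes of registration, at most 20% signal loss overall, and sufficient interpretability in the judgement of the healthcare professional (HCP). The exact duration and the signal loss "will be derived from the recordings during the analysis phase of the project, i.e. not during the measurements".
- **The repeat counts.** Section 2.1 scores the first or, when indicated, the second recording on the day of inclusion: "When the first remote eCTG measurement is reassuring but insufficient, the measurement will be repeated the same day". Section 4.4 says of an insufficient but reassuring recording that "it can be repeated once at the same day and still be considered successful".
- **Who decides on the repeat, and when.** Section 5.1 has the tracing "assessed real-time on interpretability by the HCP", and states: "Monitoring will be repeated the same day when reassuring but insufficiently interpretable, or upon request of the HCP". Section 7.3.2, for inpatients and outpatients alike, repeats a recording that is unsuccessful but reassuring.
- **Failure in the procedures.** Section 7.3.2 declares the primary outcome unsuccessful when the recording is still not interpretable after repetition on the first day. A switch to conventional CTG follows.
- **Other definitions.** The Summary defines the outcome through the need to switch to conventional CTG. The Introduction joins the signal-loss and 30-minute interpretability criteria with *or*. Section 9.1 joins them with *and/or*.
- **Disagreement is foreseen.** Section 7.1.2 counts recordings judged successful by the HCP at closure and, separately, recordings the HCP closed before the 7.1.1 criteria were met.

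**The concern.** The repeat and the score rest on different information. The HCP decides on the repeat during the measurement. Whether the 20% limit was met is established in the analysis phase, when a repeat on the same day is no longer possible. Under 7.1.1, a woman whose first recording was accepted but later shows more than 20% loss is a failure who never had the second attempt that 2.1 and 4.4 provide for. Under 7.3.2 she is not a failure, because her recording was judged interpretable and no repetition took place. The protocol does not say which applies.

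At stake is the meaning of the primary result. The target in 4.4 ("A success rate of 90% is considered clinically sufficient based on previous studies") allows for one repeat. Under 7.1.1 the observed rate would mix success after an allowed repeat with success at the first recording only. The mix would depend on when staff accept and close a recording.

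**Working it through.** **1. One recording under each section.** Take a first-day recording of 30 minutes that the HCP accepts at closure, with no switch, and that later shows 25% signal loss (25% is an illustration).

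| Protocol section | Rule | Score |
|---|---|---|
| 7.1.1 | duration, signal loss and interpretability, as a list | failure (25% exceeds 20%) |
| 7.3.2, both lists | failure only if not interpretable after repetition | not a failure |
| Summary | need to switch to conventional CTG | not a failure |
| 1 Introduction | signal loss *or* 30 interpretable minutes | success, if the HCP's judgement settles interpretability |
| 9.1 | *and/or* | undetermined |

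Section 9.1 defines signal quality as time with a fetal heart rate value. If its 30 minutes are counted that way, the recording has 30 × (1 − 0.25) = 22.5 minutes and fails on both branches. If the HCP's judgement settles the 30 minutes, it passes on the *or* branch.

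**2. The plan's figure.** Section 4.4 gives 90% success in 60 women, so 0.90 × 60 = 54 successes. Its sizing statement is "Calculated on 90% chance of success according Wilson standard error of proportions (CI95% > lower limit of 82.5%), 60 subjects are needed for inclusion". At 54/60 the two-sided 95% Wilson interval is 79.9% to 95.3%. The simple normal-approximation limit is 0.90 − 1.96 × √(0.09/60) = 82.4%, which is the one near 82.5%. That discrepancy is a separate matter and nothing below depends on it.

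**3. Direction of the bias under 7.1.1.** Among the 60 women let

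- a = first recording meets all criteria;
- b = first recording refused live, repeat meets the criteria;
- c = first recording accepted live, fails later;
- k = those among c who would have succeeded on a repeat (0 ≤ k ≤ c).

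Observed rate = (a + b)/60. Rate had the allowed repeat been offered to all of c = (a + b + k)/60. The difference is k/60, which is never negative, so the observed rate can only be too low. It is at most c/60, and c can be counted once the recordings are analysed.

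**4. Size.** Each such woman costs 1/60 = 1.67 points. The documents give no value for k; the range below is an assumption.

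| k | Successes | Rate | Wilson 95% interval |
|---|---|---|---|
| 0 | 54/60 | 90.0% | 79.9% to 95.3% |
| 1 | 53/60 | 88.3% | 77.8% to 94.2% |
| 2 | 52/60 | 86.7% | 75.8% to 93.1% |
| 3 | 51/60 | 85.0% | 73.9% to 91.9% |

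**The case against.** **The problem depends on one reading.** This is correct. If 7.3.2, the Summary or the *or* of the Introduction governs, the recording in question is not a failure and there is no bias. But 7.1.1 is the section headed as the main parameter, and both the Introduction and 9.1 refer the reader to it. The conflict itself therefore has to be resolved.

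**HCPs are trained and hold the criteria.** Sections 5.1 and 7.1.1 provide a standard operating procedure meant to prevent early closure. Section 6.4.4 says the heart rate output is suppressed when quality is too low, so gaps should be visible live. Elapsed time is visible too, which makes failure on duration less likely. This narrows the problem mainly to recordings misjudged around the 20% limit. It does not remove it, because the percentage is not derived at closure and 7.1.2 still expects premature closures.

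**Scoring real workflow is legitimate, and the bias is conservative.** Both are fair, since the objective is self-administered recording in its setting. That choice would have to be stated, however, and it would not match the repeat allowed in 4.4.

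**The analysis plan may settle scoring.** It may, but it cannot restore a repeat that was not offered.

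**Stronger readings a reader might infer.** One is that such women can never be repeated. Section 5.1 also allows a repeat at the HCP's request over the mother's or fetus's condition, although that route is not tied to signal loss. Another is to size the loss from the earlier cohort in 4.4, where (562 − 111)/562 = 80.2% of repeated tracings succeeded. That cohort used conventional CTG and counted tracings, and its rate concerns repeats that were actually made. Combined with 90% final success, it would imply first-recording failure of 0.10/0.198, about 51%, which nothing in the protocol supports. A third is to set a lowered rate against 82.5%. In 4.4 that figure is the lower limit of a confidence interval, not a threshold for the observed rate.

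**Conclusion.** The point holds in limited form. Read as a list of joint requirements, 7.1.1 turns some recordings accepted at closure into failures after the allowed repeat has lapsed, whereas 7.3.2, the Summary and the Introduction would not count them as failures and 9.1 leaves the matter open. Under 7.1.1 the bias is downward, at 1.67 points for each woman who would have succeeded on a repeat she was not offered. How many there will be cannot be derived from the documents. The conclusion assumes that 7.1.1 governs scoring and that the operating procedure, which is not at hand, gives the HCP no measured signal-loss percentage at closure, as 7.1.1 implies. It does not show that the study will miss its target.

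**What to change.** - **Reconcile** the Summary, the Introduction, 5.1, 7.1.1, 7.3.2 (both lists) and 9.1, so that one stated definition of success governs closure, the decision to repeat and the scoring. Which repeat rule to adopt is for the sponsor to decide.
- **Report** the primary result in 9.1 in three categories: success; failure after the allowed repeat; and failure on the derived criteria of a recording the HCP accepted without a repeat. Keep the third as failure in the main estimate, and give the bound with it counted as success, (a + b + c)/60 in the notation above.

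The cost is a wording change, one extra cross-tabulation and a headline result that carries a bound. Section 7.1.2 already collects the HCP's judgement at closure and the premature closures.
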